## Abstract

**Background:**

Platelet-rich plasma (PRP) contains various growth factors and inflammatory regulators, which can effectively reduce inflammation in joints and promote tissue repair. Multiple studies have proved its effectiveness in the treatment of knee osteoarthritis (KOA). Low-intensity focused ultrasound (LIFU) and transcutaneous electrical nerve stimulation (TENS) are non-invasive and safe physical therapy methods for KOA. This study is the first to propose the treatment of KOA with physical stimulation after PRP treatment, and to observe the clinical efficacy of the treatment method.

**Methods:**

This is a protocol paper that outlines a randomized controlled trial, patients will be assigned randomly to the PRP group, PRP+LIFU group, PRP+TENS group, and PRP+LIFU combined TENS group. The patients will be followed at 12-week and 24-week time points to evaluate the primary and secondary outcomes of the study. The primary outcome is the VAS pain score. Secondary outcomes include Western Ontario and McMaster Universities Osteoarthritis Index (WOMAC) and International Knee Documentation Committee scores (IKDC). After baseline examination, all patients will sign a written informed consent for study participation after a full explanation of the treatment protocol. We have planned a total of 120 patients (30 patients per group).

**Discussion:**

The objective of this clinical trial is to evaluate the effect of different physical stimulation after PRP treatment for KOA. The data will be published after the completion of the study.

**Trial registration:**

This study has been registered with the Chinese Clinical Trials Registry. Registration number: ChiCTR2200065119 (registered date: 10/28/2022).

## Administrative information

We used the SPIRIT checklist when writing our report [1].

Note: the numbers in curly brackets in this protocol refer to SPIRIT checklist item numbers. The order of the items has been modified to group similar items (see http://www.equator-network.org/reporting-guidelines/spirit-2013-statement-defining-standard-protocol-items-for-clinical-trials/).

## Introduction

### Background and rationale {6a}

One of the most prevalent conditions that affects middle-aged and elderly patients with pain and functional limitations is knee osteoarthritis (KOA), which places a heavy financial burden on patients, families, and society [2]. More than 250 million people worldwide are affected by KOA, and especially older adults over 60 have more severe symptoms of KOA [3–6]. The current treatment options for KOA include joint replacement, physical therapy, medication therapy, and health education [7, 8]. The main goals are to reduce discomfort and enhance joint performance. But the current treatment approaches are still inadequate [9].

Platelet-rich plasma (PRP) is platelet concentrate obtained by centrifugation of autologous blood, and it is widely used in regenerative medicine [10–13]. PRP is rich in growth factors, such as transforming growth factor (TGF-β), platelet-derived growth factor (PDGF), insulin growth factor (IGF), epidermal growth factor (EGF), and vascular endothelial growth factor (VEGF) [14]. PRP can control immunological and inflammatory reactions as well as aid in the regeneration and repair of blood vessels and tissues [15]. Basic study demonstrates that the mechanism of PRP applied to repair cartilage damage includes enhancing cartilage biomechanical qualities, stimulating chondrocyte proliferation, and increasing extracellular matrix formation [16]. Additionally, PRP can successfully restore damaged bone and cartilage, according to clinical studies [17, 18]. Chu et al. performed a prospective, parallel-group, double-blind, multi-center, sham-controlled randomized clinical trial demonstrated that PRP was superior to sham saline in treating KOA [19]. Also, there is solid evidence for the therapy of rotator cuff tendinopathy, and lateral epicondylitis [20–25].

For many years, the use of low-intensity focused ultrasound (LIFU) and transcutaneous electrical nerve stimulation (TENS) as physical treatments for KOA patients have been researched [26–28]. TENS and LIFU are non-invasive, drug-free methods. They are simple to use and have no unfavorable side effects. Through a thermal mechanism, ultrasound therapy may raise the pain threshold while increasing capillary permeability and tissue metabolism [29, 30]. Jia et al. performed a randomized, double blind, placebo-controlled trial that demonstrated LIFU relieving pain and improving the functions and quality of life of patients with KOA [27]. The effects of ultrasound on pain alleviation and functional improvement were described in several systematic reviews [31, 32]. Electrical stimulation reduces pain perception using the gate-control theory mechanism, which Melzack and Wall suggested in their 1965 TENS invention [33]. A study by Shimoura K et al. found TENS improved the VAS score for pain and the distance walked in the 6MWT for individuals with KOA [34]. TENS has been successfully employed in the therapeutic environment for painful KOA according to a number of randomized controlled studies [35, 36] and has been widely used in the clinical setting [37–39]. TENS and ultrasound can also be combined to lessen pain in a variety of musculoskeletal disorders [40–42]. The combination of those two physical elements has previously demonstrated good outcomes for pain alleviation and enhancing functional activity in KOA patients [43, 44].

Nonetheless, we searched the published literature so far and found no trials that combined PRP with several physical factors for conventional treatment of KOA. If the treatment of KOA with PRP combined with several physical factors selected by us achieves a good effect, then it will lay a foundation for more treatment of KOA with PRP combined with physical factors and even provide a template for more trials of regenerative therapy combined with physical factors in the future. Better treatment outcomes mean less pain and improved function and quality of life for patients, thereby reducing more of the burden on society and the health system

### Objectives {7}

The objective of this study is to assess the effectiveness and safety of utilizing LIFU, TENS, and LIFU combined with TENS after patients underwent PRP for treating KOA in this randomized controlled trial. We will evaluate how well this therapy worked for patients with KOA in terms of pain and physical function. After PRP treatment, it is hoped that the physical stimulation would help patients with knee osteoarthritis experience less pain and functional improvement.

### Trial design {8}

The study is a randomized controlled trial and has ethics approval from the West China Hospital Research Ethics Board and was registered in the research registry (ChiCTR2200065119). The study design is presented in  (Fig. 1).

**Fig. 1 Fig1:**
[figure not shown]
Summary of study design for the study

## Methods: participants, interventions, and outcomes

### Study setting {9}

Clinicians will distribute advertising flyers and recruit patients at the outpatient clinic of West China Hospital of Sichuan University, a grade III level A hospital in southwest region of China.

### Eligibility criteria {10}

Inclusion criteriaDiagnosis of osteoarthritis using the American College of Rheumatology criteriaRadiological grading of Grade I–III osteoarthritis (OA) of the knee using the Kellgren and Lawrence system

Exclusion criteriaPrevious internal and external fixation brackets after joint surgeryThe patients with local skin ulceration, infection, or local skin sensory disturbanceThe patients have used anti-inflammatory drugs in the past 2 weeks and non-steroidal anti-inflammatory drugs in the past 2 daysThe patients combined with language listening and speaking impairment or unable to cooperate with the doctor’s treatmentThe patients with a pacemakerThe patients with blood system diseases

### Who will take informed consent? {26a}

All patients will be given written explanatory materials and consent forms. The principal investigator will provide patients with sufficient information before obtaining informed consent. Once a patient is enrolled or randomized, the study site will make every reasonable effort to follow the patient for the entire study period. On the consent form, participants will be asked if they agree to use of their data should they choose to withdraw from the trial. Participants will also be asked for permission for the research team to share relevant data with people from the university taking part in the research or from regulatory authorities.

### Additional consent provisions for collection and use of participant data and biological specimens {26b}

This trial does not involve collecting biological specimens for storage. There is no anticipated harm and compensation for trial participation.

## Intervention

### Explanation for the choice of comparators {6b}

#### PRP preparation

According to the analysis of the current research, many studies reported that the most effective treatment of knee osteoarthritis is PRP with poor leukocytes [45, 46]. The PRP preparation method we use is a two-time centrifugation method. First, we will draw 45 ml blood from the vein (usually the median cubital vein) with 5 ml anticoagulant, then perform the first low-speed gradient centrifugation. After the first centrifugation, take out all the supernatants and use supernatants to perform the second centrifugation. After centrifugation, take out the upper layer, the remaining 4 ml are leukocyte-poor PRP. According to a previous study, the PRP we use contains platelets 3–8 times higher than the baseline concentration with less than or equal to the baseline concentration of white blood cells.

#### Device parameters

According to previous study the optimal transcutaneous electrical nerve stimulation at 2 Hz, 100 Hz or 2/100 Hz produced similar treatment effects for people suffering from KOA [47] and in most clinical trials the LIFU signal with a frequency of 0.6 MHz [27]. Therefore, in our trails, we set the LIFU signal at a frequency of 0.6 MHz, with a power of 100 MW/cm^2^. The TENS setting was in a conventional mode, with a frequency of 50/100 Hz. The intensity of the TENS was set at a comfortable level as determined by the participants, and the current ranged from 0 mA to 45 mA.

#### Intervention description {11a}

Eligible subjects screened by inclusion and exclusion criteria will be divided into the control group, and the experimental groups by computer randomization in a random sequence with a ratio of 1:1:1:1. The control group was treated with PRP. The experimental group was treated with PRP with LIFU, PRP with TENS, and PRP with LIFU combined with TENS. Both the experimental group and the control group received PRP treatment three times, with an interval of 4 weeks. The experimental group was treated with LIFU, TENS, and LIFU combined with TENS 24 h after each PRP treatment (the injection needles healed), once a day, for five consecutive days, for a total of three courses of treatment.

#### Criteria for discontinuing or modifying allocated interventions {11b}

The clinician will report any adverse events, and the trial steering Committee will decide whether to modify or discontinue the trial.

### Strategies to improve adherence to interventions {11c}

All participants will be informed about the procedures of the study, as well as the potential benefits and risks, so that they fully understand the importance of their participation and completion of the study. Two researchers who do not participate in allocation and evaluation will periodically review each participant’s files to make sure they are conducting the experiment properly and orderly.

#### Relevant concomitant care permitted or prohibited during the trial {11d}

Patients will be prohibited from taking pain relieving medications and receiving other intra-articular injections during the trial period.

#### Provisions for post-trial care {30}

A nurse will call the participants every 2 weeks and ask about the adverse event and patient education.

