#### Outcomes {12}

Primary outcome is WOMAC score, secondary outcomes use VAS pain score, and IKDC score were performed before each PRP treatment, 3 months, and 6 months after the end of the whole course of treatment.

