#### Adverse event reporting and harms {22}

In our study, an adverse event will be defined as any untoward medical occurrence in a subject without regard to the possibility of a causal relationship. Adverse events will be collected after the subject has provided consent and enrolled in the study. If a subject experiences an adverse event after the informed consent document is signed (entry) but the subject has not started to receive study intervention, the event will be reported as not related to the study. All adverse events occurring after entry into the study will be recorded. An adverse event that meets the criteria for a serious adverse event (SAE) between study enrollment and hospital discharge will be reported to the local institutional review board as an SAE.

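### Comparing the safety of each LIFU/TENS arm with PRP alone is open to detection bias: planned contact after each injection differs by arm, and the only timed adverse event enquiry is filed under post-trial care

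*Protocol article*

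**What the plan says.** The Objectives {7} section sets out to "assess the effectiveness and safety of utilizing LIFU, TENS, and LIFU combined with TENS after patients underwent PRP". The control arm is PRP alone, so the safety question is a comparison of each stimulation arm with that arm.

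On schedule, Intervention description {11a} says: "Both the experimental group and the control group received PRP treatment three times, with an interval of 4 weeks". Only the stimulation arms then receive device treatment "24 h after each PRP treatment (the injection needles healed), once a day, for five consecutive days, for a total of three courses of treatment". Under Outcomes {12}, the efficacy scores are taken in all arms "before each PRP treatment, 3 months, and 6 months after the end of the whole course of treatment".

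On adverse events, four places matter:

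- Adverse event reporting and harms {22}: "All adverse events occurring after entry into the study will be recorded". No method or timing of enquiry is given, and the source of an event is not distinguished.
- Criteria for discontinuing or modifying allocated interventions {11b}: the clinician reports adverse events, with no schedule.
- Plans to promote participant retention {18b}: staff follow all patients regularly, with no interval and no mention of adverse events.
- Provisions for post-trial care {30}: "A nurse will call the participants every 2 weeks and ask about the adverse event and patient education". No start, end or distinction by arm is given.

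The blinding section {17} says that participants and staff cannot be blinded; only the assessor of clinical recovery is.

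**The concern.** Adverse events are found partly by looking for them. A patient who comes for treatment on five successive days after an injection has five occasions to mention a sore or swollen knee. A patient who goes home after the injection has no scheduled occasion in those days, except a call that may or may not fall then. Short-lived reactions can come and go in that interval.

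If events from every source are put into one count, a stimulation arm could look more harmful than PRP alone because it was observed more closely. A real reduction in reactions could be masked in the same way. Unblinded staff and participants may add to this, since both know who is receiving an additional device.

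The count also matters during the trial. The interim analysis at 50% of the sample looks at risks and safety, and the steering committee may modify or stop the trial on adverse events.

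**Working it through.** The plan gives no adverse event rate or safety power figure, so there is no figure to reproduce. The check counts planned contacts and then illustrates what unequal detection can do.

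**Planned contacts per patient** (Intervention description {11a} and Outcomes {12})

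- Injections, all arms: 3. The scores before each injection are assumed to be taken at the same visit.
- Device sessions, stimulation arms only: 5 days × 3 courses = 15.
- Follow-up assessments, all arms: 2 (3 and 6 months).
- PRP alone: 3 + 2 = 5.
- Each stimulation arm: 3 + 15 + 2 = 20.
- Ratio: 20 / 5 = 4.

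This treats each session as attended by staff, which the text implies but does not state. All 15 extra contacts fall on roughly days 1 to 5 after an injection. In those days the count is 15 against 0, apart from any two-weekly call.

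**Effect of unequal detection (all values assumed)**

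Observed rate = true rate × probability of detection. With the same true rate in both arms, the observed ratio is detection in the stimulation arm / detection in the PRP arm.

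| Detection, stimulation | Detection, PRP alone | Observed ratio | Expected recorded events per 30, true rate 20% |
|---|---|---|---|
| 0.9 | 0.5 | 0.9 / 0.5 = 1.80 | 30 × 0.20 × 0.9 = 5.4 against 30 × 0.20 × 0.5 = 3.0 |
| 0.9 | 0.7 | 0.9 / 0.7 = 1.29 | 5.4 against 30 × 0.20 × 0.7 = 4.2 |
| 0.9 | 0.9 | 1.00 | 5.4 against 5.4 |

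Read the other way, a true ratio of 0.5 / 0.9 = 0.56 (first row) or 0.7 / 0.9 = 0.78 (second row) would appear as no difference. The true rate cancels from the ratio, so the result depends only on the assumed detection values.

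**Can the planned calls serve as the common enquiry?** Injections are 28 days apart and calls 14 days apart; 28 / 14 = 2. A cycle with its first call on day 7 gives calls on days 7, 21, 35, 49 and 63. With injections on days 0, 28 and 56, the calls on days 7, 35 and 63 each fall 7 days after an injection. If injections keep to schedule, one call per injection can fall at the same day in every arm without adding calls.

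**The case against.** The best reply is that a common basis already exists. The harms section records all events from entry in every arm, the clinician reports events in every arm, staff follow up all patients, and the calls go to participants without distinction by arm. Calls that began only after the trial would sit badly with recording from entry, so the sentence is probably in-trial follow-up placed under the wrong checklist item. Table 1, the assessment timeline, is not visible and may list adverse event checks. An article may also leave the call script, and a formal list of safety outcomes, to the full protocol.

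Much of this stands, and it rules out several stronger readings:

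- A reader might infer that no arm is asked about events during treatment. That rests on a heading alone; the call has no stated start or end.
- A reader might infer that PRP-alone patients uniquely go about 3 months without enquiry after the third injection. The stimulation arms also have no stated visit between their last five-day course and the 3-month assessment, so the gap is nearly the same.
- The absence of a safety measure from Outcomes {12} carries little weight, because harms have their own section.
- Unequal contact is inherent in adding sessions to PRP without a sham. No formal between-arm safety test is described, and with 30 patients per arm any such comparison is imprecise.

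One thing is not answered. Even if the call is only misfiled, events it elicits would be pooled with events noticed at the daily sessions, because the harms section does not separate sources. A call at an unspecified day of a two-week cycle is also a weaker net for short-lived reactions than five daily contacts. The imbalance therefore remains, and imprecision is no reason to accept an avoidable bias.

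**Conclusion.** The point holds as a risk of detection bias in comparing each of the three stimulation arms with PRP alone. The stimulation arms share one session schedule, so comparisons among them are not affected in this way.

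The amount is unknown. What the documents support is the difference in planned contact: 15 extra sessions per patient, or 20 contacts against 5 on the assumption that staff attend the sessions. The ratio of 1.3 to 1.8 only restates assumed detection rates.

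It would go too far to say that event rates by arm are not comparable, that safety cannot be assessed, or that a higher rate in a stimulation arm would be due to contact alone. Recording applies to every arm, in-trial calls would give a common basis, and a higher rate could be a true device effect. The difficulty is that the data as planned may not tell these explanations apart. The correction is worth making, and the resources for it are already in the plan.

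**What to change.** 1. Reconcile Provisions for post-trial care {30} with Adverse event reporting and harms {22}: state that the two-weekly calls run from first injection to last follow-up in all four arms.
2. Time one call at the same day after each injection in every arm, for example day 7, and link it to the actual injection date if an injection is delayed. Ask the same fixed questions each time, covering the whole period since the injection.
3. Use events elicited by these calls as the main basis for the between-arm safety comparison, including at the interim look.
4. Record the source of each event. Tabulate events noted only at LIFU/TENS sessions separately, and still report all of them.

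The cost is protocol wording, a short call script and one source field on the case report form; the nurse and the calls are already planned. Some calls are re-timed, and session-only events do not enter the main comparison. The change equalises the enquiry. It does not remove differences in what unblinded participants choose to report, which should be named as a limitation. Treatment is unchanged.

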#### Outcomes {12}

Primary outcome is WOMAC score, secondary outcomes use VAS pain score, and IKDC score were performed before each PRP treatment, 3 months, and 6 months after the end of the whole course of treatment.

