#### Sample size {14}

The sample size of this study was calculated according to the uniform standard of clinical trial report and the requirement of non-inferior experiment sample content. Experimental studies have shown that the minimum clinical significance value of WOMAC scale is 12%. Based on the previous research results of our research team, we set *σ* = 28%, *β* = 0.2, power = 80%, and significance level two-tailed *α* = 0.05. In order to prevent excessive loss of subjects, the shedding rate of 10% was calculated. A total of 120 subjects (27 per group, 4 groups, 10% shedding rate) were required. ITT analysis strategy will be adopted for data analysis. Paired *T*-test analysis will be performed on the evaluation data of OA patients before and after treatment, and variance analysis will be performed on the difference analysis among multiple groups.

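### The Abstract makes VAS pain the primary outcome and the Outcomes section makes it WOMAC, so the protocol does not fix the confirmatory endpoint

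*Protocol article*

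**What the plan says.** The protocol article assigns the primary role twice, to different instruments.

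- **Abstract, Methods:** "The primary outcome is the VAS pain score". The next sentence reads "Secondary outcomes include Western Ontario and McMaster Universities Osteoarthritis Index (WOMAC) and International Knee Documentation Committee scores (IKDC").
- **Outcomes {12}:** "Primary outcome is WOMAC score, secondary outcomes use VAS pain score", with IKDC also secondary.

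The sample size calculation uses WOMAC: "Experimental studies have shown that the minimum clinical significance value of WOMAC scale is 12"%. No corresponding difference or standard deviation is given for VAS.

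The two places also describe the assessment times differently. The Abstract has "The patients will be followed at 12-week and 24-week time points to evaluate the primary and secondary outcomes of the study". Outcomes {12} has the scores "performed before each PRP treatment, 3 months, and 6 months after the end of the whole course of treatment".

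**The concern.** VAS and WOMAC swap roles between the two statements, so they cannot both be right. A confirmatory trial has one main claim, and here that claim depends on which sentence is followed.

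Two things are at stake. First, if the choice stays open until results are known, the better of two correlated endpoints can be presented as the planned one, and the nominal 5% error rate no longer holds. Second, even a team acting in good faith would be open to a charge of outcome switching, because this article could be cited as pre-specification for either endpoint. The justification of the sample size is affected too: if VAS is the intended primary, the trial was sized on a different variable.

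**Working it through.** **1. Does any other section settle it?**

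| Section | What it shows | Settles it? |
|---|---|---|
| Abstract, Methods | VAS primary; WOMAC and IKDC secondary | States one answer |
| Outcomes {12} | WOMAC primary; VAS and IKDC secondary | States the opposite |
| Objectives {7} | Pain and physical function named together | No, fits either |
| Sample size {14} | WOMAC difference of 12%, SD 28% | Points to WOMAC but does not call it primary |
| Statistical methods {20a} | Same Wilcoxon and Kruskal–Wallis tests for all three scores | No, none is singled out and no multiplicity rule is given |
| Non-adherence and missing data {20c} | Mentions a primary analysis | No, its endpoint is not named |
| Protocol version | The stated reason for amendment is the move to four groups | No, it does not mention the endpoint |

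The amendment history does not explain the conflict, so it is not a trace of superseded wording.

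**2. The plan's own sample-size figure.** The dropout step reproduces: 27 × 4 = 108, and 108 / 0.90 = 120. The 27 per group does not follow from the stated WOMAC inputs. For two means, two-sided α = 0.05 and 80% power, n = 2 × 28² × (1.960 + 0.842)² / 12² ≈ 85.5, so 86 per group. That is a separate problem, and the present point does not depend on it. What matters here is that the inputs are for WOMAC. No sample size can be computed for VAS as primary, because the article gives no VAS difference or SD.

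**3. Size of the error if the endpoint is chosen afterwards.** Suppose each endpoint is tested at 0.05, there is no true effect, and a claim is made if either test succeeds. IKDC is secondary in both statements, so only two endpoints are in play.

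- Independent endpoints: 1 − (1 − 0.05)² = 0.0975.
- Correlated endpoints: the article gives no correlation ρ, so a range is shown. A four-group omnibus test has 3 degrees of freedom, and the Kruskal–Wallis statistic follows the same limiting distribution. The 3-df column comes from 1,000,000 simulated pairs of statistics per value of ρ. The 1-df column is a single pairwise contrast, from 2,000,000 pairs.

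| Assumed ρ | P(either p < 0.05), 3-df omnibus | P(either p < 0.05), 1-df contrast |
|---|---|---|
| 0 | 0.098 | 0.098 |
| 0.5 | 0.092 | 0.091 |
| 0.7 | 0.085 | 0.083 |
| 0.8 | 0.079 | 0.078 |
| 0.9 | 0.072 | 0.071 |

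Simulated F tests on four groups of 27 (200,000 replicates) agree: 0.092 at ρ = 0.5, 0.086 at 0.7 and 0.071 at 0.9. Against 0.05, that is an excess of 0.092 / 0.05 − 1 = 84% at ρ = 0.5 and 0.071 / 0.05 − 1 = 42% at ρ = 0.9.

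**The case against.** The strongest reply is that this is only a slip in the Abstract. Outcomes {12} is the operative section, an abstract merely summarises it, and the sample size uses WOMAC. Two body sections therefore outweigh one summary sentence. The trial is also registered, and the registry entry or an analysis plan, neither of which is shown, may already fix the endpoint. On that view, post hoc choice is a possibility and not a stated plan, and the 8 to 9% applies only if someone tests both endpoints and claims the winner.

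Much of this is fair. WOMAC is the likelier intention. The error rate is conditional on selective use and on an assumed correlation. The absence of VAS inputs matters only if VAS is the real primary.

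It does not remove the contradiction. The sample size section never calls WOMAC primary, and the statistical sections name no primary endpoint. Nor is this detail that an article may leave to a fuller document: the article makes two incompatible statements, and any analysis plan could agree with only one of them.

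**Conclusion.** The concern holds, and the text is wrong as written. The article names two different primary outcomes and gives no rule for choosing between them. It must be corrected before analysis because the trial's main conclusion depends on it.

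If the ambiguity were exploited, the type I error would be about 8 to 9% for an assumed correlation of 0.7 to 0.5, and about 7% at 0.9, against a nominal 5%. The existence of the contradiction rests on no assumption; only its numerical size does. That WOMAC was intended is a reasonable inference from Outcomes {12} and the sample size section. The registry should confirm it.

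**What to change.** - State one primary outcome in identical terms in the Abstract and Outcomes {12}. WOMAC is the consistent choice, being named in Outcomes {12} and used for the sample size. List VAS pain and IKDC as secondary in both places.
- Say which WOMAC score is meant. The article does not specify total or subscale. The total score is the natural reading, but the sponsor should confirm it.
- In the same sentence, name the primary time point and its origin, since the Abstract and Outcomes {12} describe follow-up differently.
- Compare the result with the registry entry before any outcome data are analysed, and record the outcome of that check with its date.

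**Cost:** if the registry also names WOMAC, this is a one-line correction of the Abstract plus the clarifications above. No visit, procedure or sample-size figure changes. If the registry names VAS, moving to WOMAC is itself a change of primary outcome, to be justified and dated before the data are seen. Keeping VAS would require a sample-size justification with a VAS difference and SD.

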### Statistical methods

#### Statistical methods for primary and secondary outcomes {20a}

All the data will be recorded in the case report form and data analyses will be done using the SPSS statistical software. Analysis of variance is used for comparing mean values of patients’ age, weight, height, and body mass index. Non-parametric measures are WOMAC, VAS, and IKDC, and differences between baseline and post-treatment scores for each group are computed by the Wilcoxon signed ranks test. The difference between each treatment group is performed by the Kruskal–Wallis test.

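### No visit is named as primary for the primary outcome, and the two descriptions of follow-up (12 and 24 weeks; 3 and 6 months after the course) are not reconciled

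*Protocol article*

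**What the plan says.** The Outcomes section has the primary and secondary scores "performed before each PRP treatment, 3 months, and 6 months after the end of the whole course of treatment". That makes five assessments, four of them after baseline: before the second injection, before the third, and at 3 and 6 months. None is singled out.

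The Abstract (Methods) describes follow-up differently: "The patients will be followed at 12-week and 24-week time points to evaluate the primary and secondary outcomes of the study". It gives no starting point and does not rank the two times.

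The Intervention description fixes the length of the course. For PRP: "Both the experimental group and the control group received PRP treatment three times, with an interval of 4 weeks". For physical stimulation, in the three experimental arms only: "24 h after each PRP treatment (the injection needles healed), once a day, for five consecutive days, for a total of three courses of treatment".

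The statistical methods add no visit. Within groups, "differences between baseline and post-treatment scores for each group are computed by the Wilcoxon signed ranks test"; between groups, "The difference between each treatment group is performed by the Kruskal–Wallis test". The Sample size section gives one two-sided significance level of 0.05 and names no visit.

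The primary outcome itself also differs. The Abstract says "The primary outcome is the VAS pain score"; the Outcomes section says "Primary outcome is WOMAC score, secondary outcomes use VAS pain score", and the sample size is built on WOMAC.

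**The concern.** A primary outcome is defined by what is measured and when. Here the second half is missing wherever it would normally stand: the Abstract, the Outcomes section, the Sample size section and the statistical methods. With two follow-up visits and one significance level, the analyst could test both and rest the conclusion on the more favourable one. A single 0.05 test would then no longer describe the error rate.

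The starting point matters for a different reason. Depending on where the Abstract's weeks begin, its first follow-up visit falls either a few weeks or about three months after treatment ends. The first reading asks about a short-term effect, the second about a sustained one. A reader of the final report needs to know which was planned.

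**Working it through.** The protocol states no error rate or visit calendar to reproduce, so both are derived from its own entries.

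**Visit calendar.** Take the first injection as day 0, one month as 91.3/3 days (so 3 months = 91.3 and 6 months = 182.6 days), and the schedule from the Intervention description.

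- Injections: days 0, 28 and 56.
- Last stimulation block (experimental arms): five daily sessions starting 24 h after day 56, so days 57–61.
- If the end of the course is read arm by arm, it is day 56 for PRP alone and about day 61 for the other arms, a difference of 61 − 56 = 5 days.

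| Visit (Outcomes section) | Course ends day 56 | Course ends day 61 |
|---|---|---|
| 3 months after the course | (56 + 91.3)/7 = week 21.0 | (61 + 91.3)/7 = week 21.8 |
| 6 months after the course | (56 + 182.6)/7 = week 34.1 | (61 + 182.6)/7 = week 34.8 |

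Compare the Abstract's 12 and 24 weeks under two readings.

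1. *Counted from the first injection (or randomisation, within 48 h of it).* The gaps are 21.0 − 12 = 9.0 to 21.8 − 12 = 9.8 weeks for the first visit, and 34.1 − 24 = 10.1 to 34.8 − 24 = 10.8 weeks for the second: about 9–11 weeks overall. Week 12 is day 84, which is 84 − 56 = 28 days after the third injection and 84 − 61 = 23 days after the last session.
2. *Counted from the end of the course.* 12 weeks is 84 days against 91.3, a gap of 7.3 days; 24 weeks is 168 days against 182.6, a gap of 14.6 days. The schedules then agree to within about 1–2 weeks.

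**Error rate with no primary visit.** Suppose each visit gets an uncorrected global test of the four arms at 0.05, and one significant visit is enough. If visits were independent, the chance of at least one false positive would be 1 − 0.95^k:

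- k = 2: 1 − 0.95² = 9.75%
- k = 4: 1 − 0.95⁴ = 18.5%

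Repeated scores in the same patients are correlated, so these are upper reference values. The protocol gives no correlation; a common value ρ between visits is assumed. The four-arm test at each visit is represented by its large-sample chi-square with 3 degrees of freedom, built from three normal contrasts that each have correlation ρ across visits (200,000 simulated trials with no arm difference):

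| Assumed ρ | Two follow-up visits | Four post-baseline visits |
|---|---|---|
| 0.5 | 9.1% | 15.9% |
| 0.7 | 8.5% | 13.4% |
| 0.9 | 7.1% | 9.6% |

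With one outcome at one named visit, the global test stays at 5%.

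**The case against.** The strongest reply is that the Abstract merely abbreviates the Outcomes section: 12 weeks is roughly 3 months and 24 weeks roughly 6, so there is one schedule. That reading is plausible and the text does not exclude it. A reader might infer a flat contradiction between the two places, but the Abstract gives no starting point, so none is shown. Table 1, the timeline, could not be seen in the text available and may supply the starting point. What stands is that the visible text leaves two readings open, about 9–11 weeks apart on one of them.

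A reader might also count four chances of success. Two of those visits are mid-course, before the second and third injections. The Abstract evaluates outcomes at the two follow-up times, and the methods speak of scores after treatment; neither clearly plans an efficacy test mid-course. The two-visit figure is therefore the main one, and the four-visit figure applies only if mid-course scores are tested as well.

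A third inference is that follow-up starts on a different day in different arms. The Outcomes section does not define the end of the course by arm. Even read that way, the offset is about 5 days in roughly 91 or 183, and no bias from it has been shown.

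Finally, multiplicity rules may sit in an analysis plan that is not at hand, and no passage says that any one significant visit will count as success. That is fair, and it makes the error rates conditional. It does not answer the main point: the primary time point is part of the primary outcome's definition and belongs in the protocol. A timeline that only lists visits would not make one of them primary.

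**Conclusion.** The point holds in this form: the text names no primary visit, and the Abstract's follow-up times have no starting point that ties them to the Outcomes section. If both follow-up visits are tested at 0.05 without correction, the false-positive rate is about 7–9%; with the mid-course visits added it is about 10–16%. Both ranges rest on assumed correlations of 0.5–0.9 and on one significant visit being enough. They are per outcome: the unresolved choice between VAS and WOMAC would add to them.

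The schedules are unreconciled rather than proven to conflict. The possible 5-day offset between arms is a minor by-product of the undefined starting event.

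**What to change.** Before outcome data are analysed:

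1. Reconcile the Abstract (VAS) with the Outcomes and Sample size sections (WOMAC), so that there is one primary outcome.
2. Name one follow-up visit, either the 3-month or the 6-month visit, as its single primary time point. Nothing in the text favours one over the other, so this is the sponsor's choice.
3. Label all other visits, including the mid-course ones, as secondary, and name the visit to which each between-group and within-group test refers.
4. State one starting event for follow-up that is the same in all four arms, for example randomisation or the third PRP injection. This also removes the possible 5-day offset.
5. Make the Abstract, the Outcomes section and Table 1 agree on times and starting event.

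The visits are already planned, so the change is mainly wording. If visits were being booked from each arm's own last treatment day, a common starting event could shift some of them by about 5 days. The statistical cost is that the follow-up visit not chosen loses confirmatory status.
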